# Efficacy and safety of switching from febuxostat to dotinurad, a novel selective urate reabsorption inhibitor, in hyperuricemic patients with type 2 diabetic kidney disease: Protocol for a single-arm, open-label, prospective, exploratory study

**DOI:** 10.3389/fendo.2022.1042061

**Published:** 2023-01-11

**Keywords:** febuxostat, dotinurad, type 2 diabetic kidney disease, urate excretion transporter, serum urate, protocol, indoxyl sulfate

## Abstract

**Background:**

Dotinurad is a novel uricosuric drug in Japan with selective and potent urate transporter 1 (URAT1) inhibitory activity. This study aims to evaluate the efficacy and safety of dotinurad in hyperuricemic patients with type 2 diabetic kidney disease by comparing serum levels of urate and plasma and urinary levels of indoxyl sulfate excreted *via* the urate excretion transporter ATP binding cassette subfamily G member 2 (ABCG2), as indices, with baseline levels after switching from febuxostat to dotinurad.

**Methods:**

This single-center, single-arm, open-label, prospective, exploratory study aims to evaluate the effect of switching from febuxostat to dotinurad on serum urate levels and its background factors. The study will include 50 hyperuricemic patients with type 2 diabetic kidney disease and urate levels exceeding 6 mg/dL despite administration of febuxostat 20 mg/day for at least 3 months. The primary outcome is the achievement rate of serum urate levels of ≤6 mg/dL after 24 weeks of treatment with dotinurad at 0.5 mg to a maximum of 4 mg once daily. Secondary outcomes include the changes in serum urate levels, plasma and urinary indoxyl sulfate levels, and renal injury-related markers from baseline to observation points at weeks 4, 12, and 24.

**Discussion:**

The study hypothesizes that switching to dotinurad may reduce the plasma levels of indoxyl sulfate and increase its urinary levels in patients with hyperuricemia. These suggest that dotinurad can potently lower the serum urate level by inhibiting URAT1 without adversely affecting ABCG2. Thus, findings of this study are expected to provide useful insights into the treatment of hyperuricemia associated with type 2 diabetic kidney disease and the discovery of new possibilities for dotinurad.

**Ethics and Dissemination:**

Prior to the study, its study protocol was scientifically and ethically reviewed and approved by the Japan Physicians Association Clinical Research Review Board (approval number: JPA007-2204-02). In addition, patients who provide written informed consent will participate in the study. The results of this study will be published through submission to a peer-reviewed scientific journal.

**Clinical trial registration:**

https://jrct.niph.go.jp/en-latest-detail/jRCTs031220080, identifier jRCTs031220080.

## 1 Introduction

The incidence of gout is increasing every year in Japan, with an estimated 1.1 million patients according to the Comprehensive Survey of Living Conditions, while the number of patients with hyperuricemia is approximately 10 million or more (1). In recent years, it has been shown that hyperuricemia not only causes gout but is also closely related to lifestyle-related diseases, such as hypertension, type 2 diabetes, and atherosclerosis, even in asymptomatic patients and may be associated with the onset and progression of chronic kidney disease (CKD) (2–4). In particular, type 2 diabetes is often complicated by hyperuricemia, and patients with these diseases have a significantly increased risk of developing CKD compared with those without hyperuricemia (5). Furthermore, high serum urate levels are a possible risk factor for CKD progression in patients with type 2 diabetic kidney disease; however, there are few reports on this possibility.

Hyperuricemia is classified into reduced urate excretion, renal overload (urate overproduction and reduced extra-renal excretion), and mixed types. The prevalence of hyperuricemia is approximately 60% for the reduced excretion type, 30% for the mixed type, and 10% for the renal overload type; hyperuricemia with reduced excretion features accounts for the majority of cases (1). This is likely due in part to the progression of CKD and a decreased glomerular filtration rate (GFR): an increase in urate levels with a decrease in urate excretion. Currently, urate-lowering drugs include xanthine oxidoreductase (XOR) inhibitors, which inhibit urate production, and uricosuric drugs; however, XOR inhibitors are recommended for patients with renal impairment, regardless of the type of hyperuricemia (1, 6).

Urate excretion transporters include URAT1, located in the proximal tubules of the kidney and is responsible for urate reabsorption, and ABCG2 and organic anion transporter 1 (OAT1) and OAT3, which are involved in excretion (7, 8). ABCG2 exits in the kidney and the intestinal tract and secretes urate (9). These urate excretion transporters are involved in the renal excretion of both urate and indoxyl sulfate, a uremic substance (10). Uremic substances accumulate in the blood and various organs and are risk factors for cardiovascular complications and other problems as well as progression to CKD (11). Furthermore, the XOR inhibitor febuxostat and the uricosuric drug benzbromarone inhibit ABCG2-mediated urate transport (12); in a previous study, febuxostat or benzbromarone increased the plasma levels of ABCG2-probe substance in rats (13). Therefore, in patients with hyperuricemia complicated by renal impairment, urate-lowering drugs that do not affect urate excretion transporters are expected to provide potent urate reduction and to reduce the progression of renal disease and the development of cardiovascular disease.

Dotinurad is a novel selective urate reabsorption inhibitor (SURI) that selectively and potently inhibits URAT1 but with little effect on ABCG2, OAT1, or OAT3 (14). However, to the best of our knowledge, the efficacy and safety of switching from the XOR inhibitor febuxostat to dotinurad in hyperuricemic patients under clinical conditions have not yet been investigated.

## 2 Methods and analysis

### 2.1 Design

The SWITCH SURI Study (efficacy and safety of SWITCHing from febuxostat to dotinurad, a novel Selective Urate Reabsorption Inhibitor, in hyperuricemic patients with type 2 diabetic kidney disease) is a single-center, single-arm, open-label, prospective trial. This is an exploratory study aimed at evaluating the effect of switching from febuxostat to dotinurad on the serum urate levels and renal impairment parameters, as well as the underlying factors and to evaluate the incidence of adverse events and changes in safety measures, such as liver enzymes, glucose, and metabolism (**Table 1**). This study will evaluate the rate of achievement of serum urate levels to ≤6 mg/dL at week 24 after switching to dotinurad.

**Table 1 T1:** Overview of All Visits and Tests Schedule.

Item	At informed consent	Observation period				At discontinuation
		Week 0	Week 4	Week 12	Week 24	
Permitted ranges of visits		0	±2 weeks	±4 weeks	±4 weeks	–
Informed consent	✓					
Demography	✓					
Study drug adherence			✓	✓	✓	✓
Concomitant therapy status		✓	✓	✓	✓	✓
Height, body weight		✓	✓	✓	✓	✓
Blood pressure, pulse rate		✓	✓	✓	✓	✓
Hematology tests		✓	✓	✓	✓	✓
Urinalysis		✓	✓	✓	✓	✓
Adverse events			✓	✓	✓	✓

Dotinurad will be started with Urece^®^ 0.5 mg tablet orally once daily within 1 week after the end of the baseline examination, and if the urate level remains above 6 mg/dL after ≥2 weeks, the dose of Urece^®^ tablets will be gradually increased (up to 4 mg), at observation points and at other scheduled visits, and continued until week 24 of the observation period.

Because of the potential to affect the evaluation of this study, the concomitant use of urate-lowering drugs (other than dotinurad), drugs that act on urate transporters (sodium-glucose cotransporter 2 [SGLT2] inhibitors, losartan, irbesartan), or drugs that affect indoxyl sulfate levels (spherical adsorptive carbon) is prohibited until the patient visit at 24 weeks after the start of dotinurad administration (except in case of discontinuation). However, in principle, drugs that patients already take before they provide consent may be continued from the date of consent until week 24, and the dosage and administration should be increased or decreased as appropriate according to medical conditions. Moreover, drugs deemed medically necessary may be added, except for the above prohibited concomitant medications.

### 2.2 Sample selection

Patients with type 2 diabetic kidney disease and hyperuricemia with urate levels exceeding 6 mg/dL even after receiving febuxostat 20 mg/day for at least 3 months who meet inclusion criteria and do not conflict with exclusion criteria will be eligible.

#### 2.2.1 Inclusion criteria

Patients with serum urate levels greater than 6.0 mg/dL and less than 10 mg/dL within 8 weeks before the day of consentPatients with type 2 diabetes mellitusPatients on febuxostat 20 mg/day for at least 3 months who have not changed their diabetes medication dosage from at least 8 weeks before the day of consent until the day of consentPatients with renal impairment within 8 weeks before the date of consent and renal function between 30 and 60 by eGFR (mL/min/1.73 m^2^)Patients with eGFR measurement data available from 6 months ( ± 2 months) before the day of consentPatients aged ≥20 years on the day of informed consent (either sex)Patients who have provided their written informed consent to participate in this study.

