### 2.3 Outcome assessment

#### 2.3.1 Primary outcome

The primary outcome of this study will be the rate of achievement of serum urate levels of ≤6 mg/dL at week 24 of dotinurad treatment.

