#### 2.3.4 Exploratory outcomes

The exploratory outcomes will include the following items.

Changes in urinary levels of urate and indoxyl sulfateInflammation oxidative stress markets: changes in serum high sensitive C-reactive protein (hs-CRP) and in urinary 8-hydroxydeoxyguanosine (8-OHdG)Comparison between groups of patients who achieved and did not achieve serum urate levels of ≤6 mg/dL (baseline levels and changes)

Two analysis groups will be set for the efficacy of this study: Full analysis set (FAS) and per-protocol set (PPS), with FAS being the primary analysis. The FAS will be the population of eligible patients who have received the study drug and have serum urate readings at baseline and at least one time point during the observation period. The PPS will be the population from the FAS excluding the participants who deviated from the study protocol (e.g., use of concomitantly prohibited drugs or study drug adherence of <80%). The Safety Analysis Set (SAS) analysis population will be established for the safety of the study, and the SAS will be the population in which the study drug is administered and data on any of the safety outcomes are obtained.

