### 2.5 Statistical analysis

Summary statistics of the background data of the study participants will be calculated. For nominal variables, the numbers in each category and their percentages will be shown; for continuous variables, the numbers, mean, standard deviation, minimum, median, and maximum values will be calculated.

The two-sided 95% confidence interval for the primary efficacy outcome of achieving a serum urate level of ≤6 mg/dL at week 24 of dotinurad treatment will be calculated, and a one-sample population proportion test will be performed for the null hypothesis of an achievement rate equal to 30%. Subgroup analysis will be performed by other candidate factors, such as subject background, to examine their impact on the primary outcome. For the secondary outcomes obtained from the metric data, summary statistics will be calculated at each observation point, a one-sample t-test or Wilcoxon’s signed rank test will be performed to evaluate their statistical significance, and if necessary, analysis of covariance and multivariate analysis will be performed. If the data are non-normally distributed, appropriate data transformations will be applied. When statistical tests are conducted, the significance level will be set at 0.05 two-sided, with the confidence coefficient for statistical estimation being 95% two-sided. Missing data in efficacy will be imputed using the last observation carried forward method.

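### Urate above 6.0 mg/dL is required before consent but not at Week 0, so patients already at target can count as achievers and inflate the single-arm rate

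*Protocol article*

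**What the plan says.** **Entry.** Section 2.2 describes "hyperuricemia with urate levels exceeding 6 mg/dL even after receiving febuxostat 20 mg/day for at least 3 months", with no date for the reading. Section 2.2.1 supplies the window: "Patients with serum urate levels greater than 6.0 mg/dL and less than 10 mg/dL within 8 weeks before the day of" consent.

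**Start of treatment.** Table 1 (section 2.1) schedules blood tests at a separate Week 0 visit. Dotinurad then starts "orally once daily within 1 week after the end of the baseline examination". The start does not depend on the urate found at that examination.

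**Analysis sets.** Section 2.3.4 requires FAS patients to "have serum urate readings at baseline and at least one time point during the observation period". The baseline reading must exist, but its value is not restricted. The PPS is formed by "excluding the participants who deviated from the study protocol (e.g., use of concomitantly prohibited drugs or study drug adherence of <80" percent); a Week 0 urate at target is not among the examples.

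**Endpoint and test.** The primary outcome is "the rate of achievement of serum urate levels of ≤6 mg/dL at week 24 of dotinurad treatment", whatever the Week 0 value. Section 2.5 states that "a one-sample population proportion test will be performed for the null hypothesis of an achievement rate equal to 30" percent, and fills missing efficacy values by last observation carried forward. Section 2.4 derives the 30% from a 20% achievement rate on febuxostat 40 mg and mentions no allowance for patients who start at target.

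**The concern.** The cut that selects patients (above 6.0 mg/dL) is also the cut that defines success (6 mg/dL or below). When patients are chosen because a reading lay above a cut, some will lie below it at the next reading with nothing changed. A single-arm trial has no control group in which to see how many.

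The study sets out to evaluate the effect of switching in patients not controlled on febuxostat 20 mg/day. A patient at or below 6 mg/dL at Week 0 is not in that state at the time of the switch. If that patient is also at or below 6 at week 24, the stated rules still count an achievement. The week-24 rate can then contain patients who were at target before the switch, and the comparison with 30% does not separate them out.

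**Working it through.** **Step 1: the plan's own figure.** Section 2.4 gives 44 patients for 90% power at two-sided 0.05 against 30%, without an expected rate. With the exact binomial and an upper tail of at most 0.025, 44 patients need at least 20 achievers (tail 0.0218). Power is 90.1% at a true rate of 54% and 92.2% at 55%. So 44 is obtainable with an unstated expected rate of about 54–55%. At the target of 50 the rule is at least 23 achievers: P(X ≥ 23 | 50, 0.30) = 0.0123, whereas 22 gives 0.0251, just over 0.025.

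**Step 2: share at target at Week 0 with no treatment change.** Model: reading = patient mean + independent within-patient variation, both normal.
- Assumed, not in the documents: total SD 1.0–1.4 mg/dL, within-patient SD 0.3–0.7 mg/dL, selection on one screening reading.
- From section 3: 41% and 51% at or below 6 mg/dL on febuxostat 20 mg. These are cumulative rates from other populations, used only to place the distribution. The 20% of section 2.4 (febuxostat 40 mg) serves as a sensitivity value.

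Let f = P(Week 0 ≤ 6 | 6 < screening < 10), and s = P(week 24 ≤ 6 | Week 0 ≤ 6, 6 < screening < 10) if the patient's mean urate does not change.

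| Source share | Total SD | Within SD | f | s |
|---|---|---|---|---|
| 41% | 1.4 | 0.3 | 0.081 | 0.49 |
| 41% | 1.0 | 0.5 | 0.189 | 0.47 |
| 51% | 1.0 | 0.5 | 0.235 | 0.50 |
| 51% | 1.0 | 0.7 | 0.336 | 0.51 |
| 20% | 1.4 | 0.3 | 0.043 | 0.45 |
| 20% | 1.0 | 0.7 | 0.140 | 0.33 |

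Over the grid f is about 8–34% (4–17 of 50) at source shares of 41–51%, and about 4–14% at 20%. The value of s is about 45–51% at 41–51% and lower at 20%, because the Week 0 reading at target is itself partly chance.

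**Step 3: effect on the test.** Suppose patients above 6 at Week 0 achieve exactly 30%. The overall rate is f·s + (1 − f)·0.30.

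| f | Half stay: overall rate | P(≥ 23/50) | All stay: overall rate | P(≥ 23/50) |
|---|---|---|---|---|
| 0.10 | 0.05 + 0.27 = 0.32 | 2.7% | 0.10 + 0.27 = 0.37 | 12% |
| 0.15 | 0.075 + 0.255 = 0.33 | 3.8% | 0.15 + 0.255 = 0.405 | 26% |
| 0.20 | 0.10 + 0.24 = 0.34 | 5.2% | 0.20 + 0.24 = 0.44 | 44% |

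With the simulated f and s, the probability runs from about 2% to 12% at source shares of 41–51%, and is about 2% at 20%. The reference value is 1.2%.

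**Step 4: regression alone.** If dotinurad merely matched febuxostat 20 mg in everyone, the week-24 rate would equal f. The probability of reaching 23 of 50 is at most about 0.5% in every setting except the most extreme (f = 0.336), where it is about 4.5%.

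**Step 5: what selecting on Week 0 does.** Requiring urate above 6.0 at Week 0 as well lowers the no-effect rate at week 24 from 8–34% to about 5–25% (from 19% to 12.5% at source share 41%, total SD 1.0, within SD 0.5). It also creates a no-effect change from Week 0 of about −0.02 to −0.30 mg/dL. Without that selection the expected no-effect change is zero.

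**Step 6: power in a smaller set.** With 40 patients the rule is at least 19 achievers (tail 0.0148; 18 gives 0.0320). Power is 86.7% at a true rate of 55% and 96.1% at 60%, against 92.2% and 98.4% with 50.

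**The case against.** **These patients are not automatic successes.** Section 2.1 prohibits other urate-lowering drugs during the study, so febuxostat has stopped. Such a patient must be at or below 6 at week 24, or at the last value carried forward, without it. This stands. A reader might infer that they have nothing to achieve, or take the 12–44% probabilities in Step 3 as false-positive rates. Those figures are upper bounds that assume every such patient stays at target, whereas in the same model only about half do. If more stay because dotinurad keeps them there, that is a drug effect.

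**The stated null is the overall rate.** Section 2.5 tests an overall achievement rate of 30%, not 30% among patients above 6 at Week 0. When the overall rate is truly 32–34%, rejecting the null is not a type I error. This stands too. A reader might conclude that the test loses its meaning, but regression alone rarely reaches the bar. What weakens is the reading of the rate as a switching effect.

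**The size is uncertain.** The SDs are assumed, and the 41–51% may not be the share at target at a single visit. The documents also do not say that one reading suffices; a confirmatory reading could sit in the full protocol, which is not shown, and would shrink the shares. This limits confidence in the size. The rules as printed still admit the patients.

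**Part is covered already.** Change in urate from baseline is a secondary outcome, achievers and non-achievers are to be compared on baseline levels, subgroup analyses are planned, and the single-arm design is an acknowledged limitation. None of these commits to showing how many were at target at Week 0 or the rate without them.

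**Conclusion.** The point holds in a limited form. As stated, the entry rule, treatment start, FAS and endpoint together let a patient at or below 6 mg/dL at Week 0 enter and possibly count as an achiever, with no control arm and no stated allowance in the 30%. Under the normal model and the assumed SDs, about 8–34% of patients could be in this position (about 4–14% at a source share of 20%). This raises the chance of meeting 23 of 50 from 1.2% to about 2–12% when the remaining patients achieve 30%. The achievement rate is inflated and its interpretation weakened; the documents do not support calling the test invalid. The exploratory label does not remove the issue, because the plan fixes a null value, a significance level and 90% power. The structural finding is firm; its size is not.

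**What to change.** 1. Report the number and share of patients at or below 6.0 mg/dL at Week 0 beside the week-24 achievement rate.
2. Prespecify, before data are examined, a key supportive analysis of the primary outcome in FAS patients with Week 0 urate above 6.0 mg/dL, with its 95% confidence interval.
3. For patients not yet enrolled, a Week 0 urate above 6.0 mg/dL may also be added to eligibility by amendment. Section 4 says enrolment had begun, so this cannot cover everyone.
4. Analyse change in urate from Week 0 in the full FAS.

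**Cost.** The FAS already requires a baseline urate, so no new measurement is needed. The restricted set is smaller: if 10 of 50 are removed, exact power at a true rate of 55% falls from 92% to 87%. The restriction reduces the bias without removing it, since about 5–25% no-effect achievement remains under the same assumptions. Selecting on Week 0 biases the change from Week 0 by about −0.02 to −0.30 mg/dL, which is the reason for item 4. If item 3 is adopted, patients enrolled under it carry this bias into the FAS as well, and the report should say so.

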#### 2.2.2 Exclusion criteria

Patients with severe renal impairment (eGFR of <30 mL/min/1.73 m^2^) or end-stage renal failure on dialysisPatients with unsettled post-acute gouty arthritisPatients with a history of any of the following diseases within 12 weeks before the date of consent: acute coronary syndrome, cerebrovascular disease, myocarditis, constrictive pericarditis, or severe valvular diseasePatients with hepatic impairment (aspartate aminotransferase [AST] or alanine aminotransferase [ALT] of ≥100 IU/L)Patients with a diagnosis or history of urinary tract stonesPatients diagnosed with malignancy or suspected or suspected of having malignancy (however, if the physician determines that the patient has not been treated with anticancer drugs for one year before the date of consent and does not plan to do so in the future, the patient is eligible)Female patients who are pregnant, lactating, or may be pregnantPatients receiving uricosuric drugs, SGLT2 inhibitors, losartan, irbesartan, or spherical adsorptive carbon within 8 weeks before the day of consentPatients requiring a surrogatePatients with a history of hypersensitivity to any ingredients of the dotinurad productOther patients who are judged by the investigator to be inappropriate for this study

After patient selection, the principal investigator or the subinvestigator will explain to the patients the details of the study using a consent explanation document approved by an accredited clinical research review committee and obtain their written consent. The principal investigator or the subinvestigator will also explain that consent is given freely by the study participant and that the subject will not be treated unfavorably even if he/she does not consent, and that the participant may withdraw consent at any time after consent is given if he/she changes his/her mind, and that the subject will not be treated unfavorably in such cases.

### 2.3 Outcome assessment

#### 2.3.1 Primary outcome

The primary outcome of this study will be the rate of achievement of serum urate levels of ≤6 mg/dL at week 24 of dotinurad treatment.

#### 2.3.2 Secondary outcomes

The secondary outcomes of this study will include the following from baseline to observation points at weeks 4, 12, and 24.

Change in serum urate levelsChanges in plasma indoxyl sulfateRenal impairment-related parameters: changes in eGFR, eGFR slope, serum creatinine, and urinary albumin and creatine (urine will be collected at any time and levels corrected for urinary creatine will be used)Changes in doses of the study drug used in the study

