### 2.4 Sample size calculation

The target sample size will be set at 50. To evaluate the efficacy of switching to dotinurad in the participants in the study, a threshold value of 30% was set based on the achievement rate of serum urate levels of ≤6 mg/dL (20%) with 40 mg of febuxostat. To demonstrate that the lower limit of the two-sided 95% confidence interval exceeds the threshold of 30%, a significance level of α = 0.05 (two-sided) and a power of 1-β 90%, the required sample size was calculated by a binomial probability hypothesis test, resulting in 44. Considering dropouts, the target sample size will be set at 50.

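### Urine for albumin may be collected at any hour, which adds avoidable within-patient noise to a renal secondary outcome

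*Protocol article*

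**What the plan says.** The renal item of the secondary outcomes (section 2.3.2) lists "changes in eGFR, eGFR slope, serum creatinine, and urinary albumin and creatine" and adds that "urine will be collected at any time and levels corrected for urinary creatine will be used". The outcomes are changes from baseline at Weeks 4, 12 and 24.

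The other urinary measures stand elsewhere: sodium among the safety outcomes (section 2.3.3), and urate, indoxyl sulfate and 8-OHdG among the exploratory outcomes (section 2.3.4). None has a collection time or a correction beside it. Table 1 has a single urinalysis row with one entry per visit.

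The abstract treats urinary indoxyl sulfate as more than exploratory: "Secondary outcomes include the changes in serum urate levels, plasma and urinary indoxyl sulfate levels, and renal injury-related markers". It also states the hypothesis that "switching to dotinurad may reduce the plasma levels of indoxyl sulfate and increase its urinary levels in patients with hyperuricemia".

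On timing, section 2.1 starts dotinurad as a "0.5 mg tablet orally once daily within 1 week after the end of the baseline examination", with no hour of dosing. The Table 1 row "Permitted ranges of visits" is in weeks: ±2 at Week 4 and ±4 at Weeks 12 and 24. Nothing in the article ties urine collection to a time of day or to the dose.

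**The concern.** Each patient serves as his or her own control, so the precision of a urinary change depends on how comparable the samples are from visit to visit. Albumin excretion varies with posture and activity. A ratio to creatinine allows for how concentrated the urine is, but leaves that variation in. If one sample is taken early in the day and the next in the afternoon, part of the recorded change reflects the hour and not the switch of drug.

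At stake is the precision of a renal secondary outcome. If the same urine is used for indoxyl sulfate, the urinary half of the mechanistic hypothesis is affected too. With a single arm, no comparison group would show up a drift in sampling hour.

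**Working it through.** **The plan's own figure.** There is none to reproduce. The article gives no SD, target difference or power for any urinary outcome. The 90% power and the sample size in section 2.4 concern the primary outcome only.

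**Reading the text.**

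1. The sampling rule is stated, not omitted: collection time is left free.
2. By position it covers the renal parameters, which for urine means albumin.
3. One urinalysis entry per visit makes it likely that the other analytes come from the same sample. The article does not say so.
4. *Creatine* appears twice for urine, while the same list has creatinine for serum.

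**Illustration of size.** From the article: N = 44 (required size; 50 are targeted) and two-sided α = 0.05. Assumed: 80% power, a within-patient SD *s* of the log urinary ratio at a fixed hour, and an additional SD *t* from a varying hour that is independent between visits.

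- SD of the log change = √(2(s² + t²))
- Smallest detectable log change = (1.960 + 0.842) × SD / √44 = 0.4224 × SD
- Smallest detectable rise = exp(that value) − 1
- Variance inflation = (s² + t²)/s²

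Example with s = 0.3 and t = 0.2: SD = √(2 × 0.13) = 0.510. The detectable log change is 0.4224 × 0.510 = 0.215, a rise of 24.0%.

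| s | t | SD of change | Detectable rise | Variance inflation |
|---|---|---|---|---|
| 0.3 | 0 | 0.424 | 19.6% | 1.00 |
| 0.3 | 0.2 | 0.510 | 24.0% | 1.44 |
| 0.3 | 0.3 | 0.600 | 28.8% | 2.00 |
| 0.3 | 0.5 | 0.825 | 41.7% | 3.78 |
| 0.5 | 0 | 0.707 | 34.8% | 1.00 |
| 0.5 | 0.2 | 0.762 | 37.9% | 1.16 |
| 0.5 | 0.3 | 0.825 | 41.7% | 1.36 |
| 0.5 | 0.5 | 1.000 | 52.6% | 2.00 |

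A fall may be the change of interest for albumin. The same log changes convert as 1 − 1/(1 + rise). For s = 0.3 this gives 1 − 1/1.196 = 16.4% without timing noise, 1 − 1/1.240 = 19.4% at t = 0.2 and 1 − 1/1.417 = 29.4% at t = 0.5.

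With all 50 patients and s = 0.3, the detectable rise goes from 18.3% to between 22.4% and 38.6%.

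**Noise against bias.** If the hour varies at random between visits, *t* widens the interval and leaves the mean change alone. The mean moves only if the typical hour differs between Week 0 and follow-up. The article gives no information on that in either direction.

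**The case against.** Spot urine is a practical and openly stated choice in a single-center exploratory study. The primary outcome is measured in serum, and section 2.5 already allows data transformation. Recording of sampling times may be in the full protocol. All of this stands and keeps the point small. It does not remove the point, because the article itself states the free collection time.

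Four stronger readings are tempting and are not supported.

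- **That the rule governs urinary urate and indoxyl sulfate.** The parenthesis belongs to the renal parameters. Extending it rests on the single urinalysis row. The argument from changes over the dosing day applies chiefly to urate, which lies outside the stated rule.
- **That the wrong analyte will be measured.** Albumin paired with *creatine*, in a list that has creatinine for serum, is almost certainly a misprint. The article has other slips of this kind.
- **That the urinary changes are biased.** That needs a systematic shift of hour, which the article does not show.
- **That a definite multiple of patients is lost.** Assuming an SD of 0.5 for random and 0.3 for timed samples gives (0.5/0.3)² = 2.78, but this only squares two assumptions. Within an SD range of 0.25 to 0.6 the variance ratio can lie anywhere from 1 to (0.6/0.25)² = 5.76.

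The independence of *t* between visits is also an assumption. Patients who habitually attend at the same hour would lose less.

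**Conclusion.** The point holds for urinary albumin and is minor. The article fixes a collection rule that leaves avoidable within-patient noise in an uncontrolled before-after comparison, and creatinine correction does not remove that noise. The loss could be slight (variance inflation 1.16 with s = 0.5 and t = 0.2) or substantial (3.78 with s = 0.3 and t = 0.5). The article gives no SD with which to narrow this range. Whether urinary urate and indoxyl sulfate are affected is likely but unstated. That matters most for indoxyl sulfate, because the hypothesis includes a rise in its urinary level.

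**What to change.** - In section 2.3.2, replace the free collection time with a first-morning sample, or with a sample at the same clock time for each patient at Weeks 0, 4, 12 and 24.
- Record the collection time at every visit and, after Week 0, the time of the last dotinurad dose. A rule based on time since that dose cannot cover Week 0, because dotinurad starts only after the baseline examination.
- Enrollment has started (section 4). For patients whose baseline urine is already taken, keep follow-up collection at the baseline clock time where it is known. Moving them to first-morning urine could itself create a shift between baseline and follow-up.
- State that the sampling rule and the creatinine correction apply to all urinary analytes, including those in sections 2.3.3 and 2.3.4.
- Print creatinine for *creatine* in both places.

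The cost is wording, a visit instruction and one or two recorded times. No visit or assay is added. The downside is that patients must bring a morning sample or keep a fixed appointment time.
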